### TPT Intervention

Eligible participants, clustered by epidemiologically linked index cases, will undergo 1:1 randomization through an interactive web response system into 2 arms: the intervention arm will receive a 12-dose 1H_3_P_3_ regimen, and the active control arm will receive a 90-dose 3HR regimen. Intervention discontinuation should be considered under the following circumstances: (1) at any time upon request by the participant and/or their guardian, (2) major protocol deviation, or (3) an AE deemed by the safety review committee to result in an unfavorable risk-benefit profile for the participant. Interruption of one or more drugs of the assigned regimen consecutively for ≥1 month will be considered permanent discontinuation. Table 1 shows the detailed dosage and administration protocol of study drugs in each regimen. Any dose adjustment is strictly prohibited and will be considered a protocol deviation. All medications will be provided free of charge. TPT other than the assigned intervention is prohibited during the study.

**Table 1. T1:** Dosage and administration of study drugs for the 1H_3_P_3_ (1-month isoniazid plus rifapentine 3 times weekly) and 3HR (3-month daily isoniazid plus rifampicin) regimens.

Regimen and dosing categories (age and/or weight)	Dosage			Administration	Treatment course (months)
	Isoniazid	Rifapentine	Rifampicin		
1H_3_P_3_					
Weight 30-35 kg	300 mg	300 mg	N/A^a^	3 times weekly	1
Weight ≥35 kg	400 mg	450 mg	N/A	3 times weekly	1
3HR					
Age ≥18 years					
Weight <50 kg	300 mg	N/A	450 mg	Once daily	3
Weight ≥50 kg	300 mg	N/A	600 mg	Once daily	3
Age <18 years (weight-based dosing)	10 mg/kg^b^	N/A	10 mg/kg^c^	Once daily	3

a N/A: not applicable.

b Maximum dose of isoniazid=300 mg.

c Maximum dose of rifampicin=450 mg.

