### Randomization and Sample Size Calculation

Enrolled LTBI participants linked to the same index case will be defined as a cluster [14,15], with an assumed average cluster size of 4 participants. Cluster-level randomization will be triggered when ≥1 eligible participant is enrolled within a cluster. Randomization sequences will be pregenerated by the study statistician using SAS (version 9.4; SAS Institute Inc) and will not be accessible to any personnel involved in enrollment, assignment, or intervention delivery. Designated personnel will perform centralized randomization via the interactive web response system. Randomization results will be relayed to the respective site investigators. This is an open-label study, and all participants within the same cluster will receive identical group assignments. To address intercenter heterogeneity, a 2-stage randomization strategy will be applied: in the first stage, stratification by study site will balance baseline characteristics across centers; in the second stage, permuted block randomization (block size=4) within each site will ensure immediate group balance during participant enrollment.

On the basis of surveillance data from China’s National Tuberculosis Control Program, we estimate that the 2-year cumulative active TB incidence among LTBI participants will be 7% [16,17]. Both the 3HR and 1H_3_P_3_ regimens are assumed to have 70% protective efficacy (ie, reducing the 2-year cumulative incidence of active TB into 2.1%).

The intracluster correlation coefficient (ICC) was incorporated into calculations. A systematic review reported ICC values of 0.028 (range 0.0005‐0.21) for school-based clusters [15], while the National Institutes of Health Pragmatic Trials Collaboratory suggested a range of 0.01 to 0.05 [18]. Therefore, we adopted a conservative ICC estimate of 0.05 for this study.

Using these parameters and a prespecified noninferiority margin of a 20% relative reduction in protective efficacy, a total of 396 clusters (n=1584 participants) per treatment arm are required to achieve 80% power at a 1-sided *α*=.05. This sample size is calculated to satisfy the clinically meaningful noninferiority margin, accounting for the cluster randomized design (ICC=0.05, average cluster size=4). Accounting for a 10% attrition rate to mitigate the impact of loss to follow-up on statistical power and outcome validity, each arm will enroll 1760 participants.

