### Statistical Analysis

Statistical analyses will be performed using SAS and R (R Foundation for Statistical Computing). Multiple imputation will be conducted to handle missing data, with additional inverse probability weighting applied for the nonintervention cohort to adjust for potential attrition bias. Continuous variables will be summarized as mean (SD) or median (IQR), as appropriate. Categorical variables will be summarized as counts and percentages.

The primary analysis will assess the noninferiority of the 1H_3_P_3_ regimen compared to the 3HR regimen in preventing active TB over the 24-month follow-up period, and the primary end point is the composite of bacteriologically confirmed or clinically diagnosed active TB. To account for the cluster randomized design and the inherent correlation within clusters, we will use a Cox proportional hazards regression model with shared frailty terms and exact likelihood estimation. Noninferiority of the 1H_3_P_3_ regimen relative to the 3HR regimen will be concluded if the analysis demonstrates that the 1H_3_P_3_ regimen does not experience a ≥20% relative reduction in protective efficacy for preventing active TB over the 24-month follow-up period. To enhance precision and address potential baseline imbalances despite randomization, the model will adjust for key prespecified covariates, such as age, sex, BMI, characteristics of the index case (smear or cavitation status), and cluster size. Outcomes will be assessed via 2 prespecified analyses with explicit definitions: the modified intention-to-treat population includes all randomized participants who received at least 1 dose of the study medication, analyzed by the assigned treatment group regardless of subsequent protocol deviations or treatment discontinuation; the per-protocol population includes all randomized participants who completed ≥90% of scheduled doses within 110% of the planned treatment duration without major protocol deviations (including use of prohibited concomitant anti-TB medications, enrollment despite exclusion criteria, or unblinding to outcome assessors). Prespecified subgroup analyses will examine treatment effect heterogeneity by age (13-17 years vs ≥18 years) and index case features (smear or cavitation status), tested through interaction terms in Cox models (interaction *P*<.10).

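### Both planned efficacy sets require study drug to have been taken, so randomized participants who never start are in no analysis of an open-label trial of 12 versus 90 doses

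*Protocol article*

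**What the plan says.** The protocol article settles the analysis sets itself. Under Statistical Analysis: "Outcomes will be assessed via 2 prespecified analyses with explicit definitions". The first set is defined as follows: "the modified intention-to-treat population includes all randomized participants who received at least 1 dose of the study medication". Its members stay in their assigned arm whatever happens after that dose. For the second, "the per-protocol population includes all randomized participants who completed ≥90% of scheduled doses within 110% of the planned treatment duration", and major deviations are also excluded. The article does not say which of the two is primary, and it describes no analysis of everyone randomized.

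Under Randomization and Sample Size Calculation: "This is an open-label study, and all participants within the same cluster will receive identical group assignments". Also: "Randomization results will be relayed to the respective site investigators". And: "Cluster-level randomization will be triggered when ≥1 eligible participant is enrolled within a cluster". Under TPT Intervention, "the intervention arm will receive a 12-dose 1H_3_P_3_ regimen, and the active control arm will receive a 90-dose 3HR regimen".

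Under Study Objectives and End points, the primary end point is counted over 24 months from randomization, not from the first dose. No expected share of non-starters appears anywhere. The Introduction reports poor adherence to and completion of 3HR in China, and puts this down mainly to its length and toxicity.

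**The concern.** A first-dose condition does little harm when the arm is still masked at that dose, because the assignment cannot then influence who starts. Here it can. Participants and sites may know the arm before the first dose, and the regimens differ in a feature that plausibly matters to someone deciding whether to begin. Taking a first dose is then an event after randomization that the arm may affect, and it decides who is analyzed.

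If the people who do not start differ between arms in number and in TB risk, the remaining groups are no longer the groups that randomization created. With neither planned set covering everyone randomized, nothing in the plan would show whether this had happened.

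This is separate from the question of who enrols once a cluster has been randomized. It would remain even if every cluster member consented first.

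**Working it through.** **1. Who is in which set**

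| Randomized participant | At-least-1-dose set | Per-protocol set |
|---|---|---|
| Takes at least 90% of doses on time, no major deviation | in | in |
| Starts, then stops early | in | out |
| Takes no dose | out | out |

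The planned multiple imputation fills missing values. It does not bring back people whom both definitions leave out.

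**2. The plan's own figures**

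- Treated 2-year risk: 7% × (1 − 0.70) = 2.1%, as stated.
- Margin, a 20% relative loss of efficacy: 0.80 × 70% = 56%. The risk is then 7% × (1 − 0.56) = 3.08%, and the ratio is 3.08/2.1 = 1.47.
- Attrition: 1584/0.90 = 1760, as stated. The article justifies the 10% by loss to follow-up and names no allowance for non-starters. How 1584 was reached is a separate matter and is not used here.

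**3. Inputs that must be assumed**

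Let d be the share never starting (d1 for 1H3P3, d3 for 3HR). Let r be the untreated TB risk of non-starters relative to starters, taken as equal in both arms. The ranges used are d1 = 0 to 5%, d3 = 2 to 15%, and r = 0.5, 1 or 2. The average untreated risk is held at 7%, starters get 70% efficacy, and non-starters get none. Of 1760 per arm, 1% is about 18 people, 2% about 35, 5% is 88 and 10% is 176.

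**4. Truly equal regimens**

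- Untreated risk of starters: b = 7%/[(1 − d) + d·r].
- Risk in the at-least-1-dose set: 0.3·b.
- Risk in all randomized: (1 − d)·0.3·b + d·r·b.

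Example with d1 = 2%, d3 = 10%, r = 2:

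- 1H3P3: b = 7/1.02 = 6.863%, so starters have 2.059%.
- 3HR: b = 7/1.10 = 6.364%, so starters have 1.909%.
- At-least-1-dose ratio: 2.059/1.909 = 1.078.
- All randomized: 1H3P3 is 0.98 × 2.059 + 0.02 × 2 × 6.863 = 2.292%. 3HR is 0.90 × 1.909 + 0.10 × 2 × 6.364 = 2.991%. The ratio is 0.766.

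Risk ratios, 1H3P3 to 3HR, for r = 0.5 / 1 / 2:

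| d1 vs d3 | At-least-1-dose | All randomized |
|---|---|---|
| 2% vs 2% | 1.000 / 1.000 / 1.000 | 1.000 / 1.000 / 1.000 |
| 0% vs 2% | 0.990 / 1.000 / 1.020 | 0.977 / 0.955 / 0.916 |
| 1% vs 5% | 0.980 / 1.000 / 1.040 | 0.955 / 0.916 / 0.856 |
| 2% vs 10% | 0.960 / 1.000 / 1.078 | 0.912 / 0.849 / 0.766 |
| 5% vs 15% | 0.949 / 1.000 / 1.095 | 0.891 / 0.827 / 0.760 |

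Under this model the at-least-1-dose ratio equals the true ratio of 1.00 only when non-starting is balanced (d1 = d3) or unrelated to risk (r = 1). The all-randomized ratio answers a different question, the effect of being assigned a regimen, and so it also reflects unequal uptake.

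**5. What an all-randomized analysis does to a regimen at the margin**

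Let 1H3P3 starters have 3.08%, 3HR starters 2.1%, and r = 1.

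- 1% vs 10%: (0.99 × 3.08 + 0.01 × 7)/(0.90 × 2.1 + 0.10 × 7) = 3.119/2.590 = 1.20.
- 1% vs 5%: 3.119/(0.95 × 2.1 + 0.05 × 7) = 3.119/2.345 = 1.33.
- 5% vs 5%: (0.95 × 3.08 + 0.05 × 7)/2.345 = 3.276/2.345 = 1.40.

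All three lie below the true 1.47 among starters.

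**The case against.** Four points on the other side carry weight.

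- **Non-starting may be rare.** Consent follows a full explanation of the study, decliners are offered a separate nonintervention cohort, the drugs are free, and Table 2 shows treatment beginning at day 0 alongside allocation. These points stand. They make a small number plausible, but the article does not give one.
- **The Introduction's remark on 3HR is about adherence and completion.** Someone who takes one dose and stops remains in the at-least-1-dose set. A reader might infer that 3HR participants will refuse the first dose more often. That is reasonable as a worry, but the article does not say it.
- **The numbers do not point to a false claim of noninferiority.** In every unequal scenario above, the at-least-1-dose ratio is less favourable to 1H3P3 than the all-randomized ratio. Only lower-risk 3HR non-starters would push it below the true 1.00, and then only to about 0.95.
- **The choice of set is partly a choice of question.** Study Design speaks of protective efficacy, and the Discussion leaves real-world use to later studies. This supports keeping a dose-conditioned analysis. It does not support having no other kind, since the end point clock starts at randomization.

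It might also be said that an unseen analysis plan could add the missing set. The article, however, states two analyses and defines both, so this is a stated choice and not an omitted detail.

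**Conclusion.** The point holds as a gap in the planned analyses. Both sets condition on taking drug in an open-label trial with very unequal burden, so no planned efficacy analysis keeps the full randomized comparison. This is true whichever of the two sets is primary.

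A reader might go further and infer that randomization is in fact lost by arm, that the result is tilted toward success, or that the at-least-1-dose set is the main analysis. The article supports none of these. It gives no non-start rates, the direction depends on the unknown risk of non-starters, and no set is named as primary.

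Under the assumed rates, the at-least-1-dose ratio moves between about 0.95 and 1.10 when the regimens are equal, against a margin of about 1.47. The effect is nil if non-starting is negligible, balanced, or unrelated to TB risk.

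**What to change.** - Prespecify an analysis of all randomized participants confirmed eligible at randomization, by the arm assigned to their cluster and counted from randomization, whether or not a dose was taken.
- State that non-starters stay on the existing 6-monthly follow-up. Study Design already runs it from randomization, and the Table 2 footnote allows remote contact after the intervention period.
- Report the number of non-starters by arm.
- Keep the at-least-1-dose and per-protocol analyses. Conclude noninferiority only if the all-randomized and per-protocol results agree.

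The last condition matters. Untreated participants pull the all-randomized ratio toward 1, or below it if they are concentrated in 3HR (1.47 to about 1.20 in the example above), so that set must not be the sole basis for noninferiority.

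The cost is amended wording and continued contact with what may be few people. There is still time: the article expects recruitment to run to September 2026, with analysis only after the 2-year follow-up.

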### Study Objectives and End points

The primary objective is to demonstrate noninferiority of the ultrashort course of the 1H_3_P_3_ TPT regimen compared with the standard 3HR regimen in preventing active TB, as measured by the 24-month cumulative incidence of active TB following randomization. The secondary objectives include: (1) to compare safety, patient-reported quality of life, and treatment discontinuation rates attributable to AEs between the regimens; (2) to evaluate treatment adherence using protocol-defined completion criteria; (3) to assess acquired *M tuberculosis* drug resistance among participants who develop active TB after TPT; and (4) to establish a contemporary nonintervention cohort for exploratory comparison, delineating the natural progression to active TB among individuals with high-risk LTBI in whom active TB has been ruled out.

The primary end point is a composite of bacteriologically confirmed or clinically diagnosed active TB within 24 months after randomization. Bacteriologically confirmed active TB refers to *M tuberculosis* identification via ≥1 sputum culture and/or molecular assay (eg, GeneXpert MTB-RIF) with detectable bacterial load. Clinically diagnosed TB combines objective clinical symptoms (≥2 of the following: cough ≥2 weeks, fever, night sweats, weight loss >10%, or hemoptysis) and imaging findings highly suggestive of active TB (eg, cavity or nodular lesions on chest CT), after exclusion of alternative diagnoses. Secondary end points include severity-graded AEs, treatment discontinuation (defined as any permanent cessation prior to regimen completion), treatment completion (defined as completing ≥90% of scheduled doses within 110% of the planned treatment duration), all-cause mortality, and acquired drug resistance determined by drug susceptibility testing or targeted molecular assays of *M tuberculosis* isolates from active TB cases. Exploratory analysis will use the nonintervention cohort to establish the background incidence of active TB, against which the risk reduction of each TPT regimen can be calculated. Patient-reported outcomes (PROs) will be calculated using health state utility values and EuroQol visual analog scale scores.

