For secondary end points, all AEs, serious AEs (SAEs), and treatment discontinuations due to AEs will be documented. Group differences in AE proportions will be analyzed using the chi-square test or Fisher exact test (2-sided *α*=.05). Treatment completion is defined as consuming ≥90% of planned doses within 110% of the planned treatment duration (≥11 doses within 6 weeks for the 1H_3_P_3_ group and ≥81 doses within 16 weeks for the 3HR group). The 2-year cumulative incidence of active TB in the nonintervention cohort will be calculated using the Kaplan-Meier method, with 95% CI estimated. The protective efficacy of the 1H_3_P_3_ and 3HR regimens relative to the nonintervention cohort will be quantified as the risk reduction rate: 1–(intervention group incidence/nonintervention group incidence). The Fisher exact test will be used to compare incidence differences among the 3 cohorts.

All analyses concerning the PRO end point will be explicitly restricted to the subgroup of participants who complete the EuroQol 5-Dimensions 3-level questionnaire. The baseline characteristics of this PRO subgroup will be compared between the 2 arms to confirm that randomization balance was maintained. Any interpretation of PRO findings will explicitly acknowledge their exploratory nature and the fact that they are derived from a subset of the total study population. Trends in PRO metrics over time will be visualized using line graphs, with mean values and 95% CIs plotted to illustrate group-level changes. A mixed-effects model for repeated measures will be used to compare PRO differences between the 1H_3_P_3_ and 3HR groups across time points, with fixed effects including treatment group, assessment time point, treatment group×time point interaction, age, sex, BMI, and index case cavitation status, and a random participant-specific intercept to account for within-subject correlation from repeated assessments.

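### The per-protocol set drops TB arising during dosing over about 81 days for 3HR but about 24 days for 1H3P3, which by itself pushes that analysis's hazard ratio above 1

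*Protocol article*

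**What the plan says.** All references are to the Protocol article.

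- **Per-protocol set** (Statistical Analysis): "the per-protocol population includes all randomized participants who completed ≥90% of scheduled doses within 110% of the planned treatment duration", and without major deviations. The listed deviations start with "including use of prohibited concomitant anti-TB medications" and end with "or unblinding to outcome assessors".
- **Completion thresholds** (Statistical Analysis, secondary end points): "≥11 doses within 6 weeks for the 1H_3_P_3_ group and ≥81 doses within 16 weeks for the 3HR group". TPT Intervention gives the regimens: "the intervention arm will receive a 12-dose 1H_3_P_3_ regimen, and the active control arm will receive a 90-dose 3HR regimen".
- **End point** (Study Objectives and End points): a "composite of bacteriologically confirmed or clinically diagnosed active TB within 24 months after randomization". Table 2 shows TB surveillance running continuously from allocation, so TB during dosing is an end point event.
- **Model** (Statistical Analysis): a "Cox proportional hazards regression model with shared frailty terms and exact likelihood estimation". No landmark or delayed entry is stated.
- **Other analysis set** (Statistical Analysis): the modified intention-to-treat set keeps everyone with at least one dose, whatever happens afterwards. The article does not say which of the two sets governs the noninferiority conclusion.
- **Masking**: "This is an open-label study" (Randomization and Sample Size Calculation). Suspected cases go to an independent panel for adjudication (Data Collection and Management).

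**The concern.** Entry to the per-protocol set depends on something that happens after time zero, and how long it takes differs by arm. To qualify, a participant must in effect stay free of TB until the threshold dose. Consider the same TB case found at the month 2 visit, which both arms have. On 1H3P3 dosing is already finished, so the case counts. On 3HR, 81 daily doses cannot have been taken by day 60, so if preventive dosing stops at diagnosis the participant and the event both disappear. The control arm has the longer stretch in which events cannot count, so the comparison is tilted against 1H3P3 even when the regimens protect equally.

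A per-protocol analysis is usually read in a noninferiority trial as a check on the intention-to-treat result. A built-in tilt can make the two sets disagree for a reason that has nothing to do with efficacy.

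The exclusion for unblinding of outcome assessors raises a related problem. Only suspected cases reach the panel, so this criterion can mainly remove possible events.

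**Working it through.** **Inputs from the article.** 12 doses at three per week against 90 daily doses; 90% completion; 24 months of follow-up (730 days); 2.1% incidence assumed in both arms; 1584 evaluable participants per arm; margin of a 20% relative loss of 70% efficacy.

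**Thresholds reproduced.** 0.9 × 12 = 10.8, so 11 doses; 0.9 × 90 = 81 doses. Both match the article.

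**Deletion windows.** On a three-per-week schedule, 9 doses fall in the first three weeks and the 11th falls on about day 24. The 81st daily dose falls on day 81. These are the earliest qualifying days; the article's outer limits are 6 weeks (42 days) and 16 weeks (112 days).

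**Margin as a ratio.** Efficacy 0.8 × 70% = 56%; incidence 7% × 0.44 = 3.08%; 3.08/2.1 = 1.467, and ln(1.467) = 0.383.

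**Constant hazard, true ratio 1.00.** Expected events per arm: 0.021 × 1584 = 33.3.

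- Deleted from 3HR: 33.3 × 81/730 = 3.7 (11%).
- Deleted from 1H3P3: 33.3 × 24/730 = 1.1 (3%).
- Difference: 2.6 events.
- Hazard ratio ≈ (1 − 24/730)/(1 − 81/730) = 706/649 = 1.088.
- Share of the log margin: ln(1.088)/0.383 = 0.084/0.383 = 22%.

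A simulated Cox hazard ratio (2 million per arm, equal hazards, no frailty) is 1.00 with all events kept and 1.09 to 1.10 with early events removed, which supports the approximation.

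**Other windows and timings.**

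| Case | Calculation | Hazard ratio |
|---|---|---|
| No TB on treatment | nothing deleted | 1.00 |
| Constant hazard, day 24 vs 81 | 706/649 | 1.09 |
| Constant hazard, 1 vs 3 months | 23/21 | 1.10 |
| Constant hazard, 6 vs 16 weeks | 688/618 | 1.11 |
| 40% of events in months 0–6 (assumed) | (1 − 0.4/6)/(1 − 0.4/2) | 1.17 |
| 50% of events in months 0–6 (assumed) | (1 − 0.5/6)/(1 − 0.5/2) | 1.22 |

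The last two rows spread the early events evenly over six months and round the windows to 1 and 3 months. They use ln(1.167)/0.383 = 40% and ln(1.222)/0.383 = 52% of the log margin. Nothing in the article gives the timing of events.

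**If the margin were 20 percentage points of efficacy** (70% to 50%, 3.5/2.1 = 1.667), a ratio of 1.088 would use 0.084/0.511, about one sixth of it.

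**Effect on power, roughly.** Effective events: 2 × 33.3/1.15 = 58, where 1.15 = 1 + 3 × 0.05 is the design effect. Standard error: 2/√58 = 0.263. The chance of showing noninferiority at 1.467 is Φ(0.383/0.263 − 1.645) = 0.43 at a ratio of 1.00, and Φ((0.383 − 0.084)/0.263 − 1.645) = 0.31 at 1.088. At 1.667 it goes from 0.62 to 0.49. This holds the event count fixed and ignores other exclusions.

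**The case against.** The strongest reply is that the modified intention-to-treat analysis is untouched, the tilt is conservative and it may be tiny. Active TB is excluded at entry by imaging and sputum testing, and participants take two active drugs during the window, so on-treatment TB could be rarer than a constant hazard implies. All of this stands. It limits the size, but it does not make the definition sound: the rule is stated explicitly, without an exception, and differs by arm.

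A reader might infer more than the article supports in four ways.

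- **That the trial's hazard ratio as a whole is biased.** Only the per-protocol estimate is affected, and nothing makes that set decisive.
- **That the net per-protocol bias must run against 1H3P3.** All other non-completers are dropped too. If they are at higher risk and more common on 3HR, that adds to the tilt; if they are at lower risk, it works the other way. The article does not settle this.
- **That the unblinding exclusion removes everyone, because site staff know the arm.** Site investigators screen and refer; an adjudication committee or independent panel decides the diagnosis. Open treatment with masked adjudication is coherent. What remains is that the exclusion can mainly reach suspected cases, and so selects on outcome.
- **That treating diagnosed TB counts as prohibited medication and deletes every treated case.** TPT Intervention prohibits other preventive treatment, not treatment of diagnosed disease. One clarifying phrase is enough.

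**Conclusion.** The point holds for the per-protocol analysis only. As written, the set removes on-treatment TB over about 81 days on 3HR and about 24 days on 1H3P3. With equal true hazards, this one mechanism gives a hazard ratio of about 1.09 under a constant hazard, with a floor of 1.00 and about 1.17 to 1.22 under assumed front-loading.

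The result rests on TB diagnosis ending preventive dosing before the threshold, which the article does not say outright, and on event timing, which it does not give. It is also inexact to say that only 1H3P3 can contribute events throughout months 1 to 3, since a fully adherent 3HR participant qualifies from day 81. The mechanism does not create false noninferiority; it costs power and can produce spurious disagreement between the two sets. It should be corrected, but it does not threaten the modified intention-to-treat result.

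**What to change.** 1. Define per-protocol adherence up to the earlier of regimen end or TB diagnosis: at least 90% of the doses scheduled to that date. On-treatment TB in adherent participants then stays in the set in both arms.
2. State that TB treatment started after diagnosis is not a protocol deviation for this set.
3. As a check, repeat the analysis with both arms landmarked at a common month 4, after the 16-week limit. This addresses only TB after that point, so it supports the main per-protocol analysis and does not replace it.
4. Remove unblinding of outcome assessors from the exclusions, and handle any unmasked adjudication in a sensitivity analysis.

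These changes remove the unequal window; they do not remove selection from dropping other non-completers. The cost is protocol or SAP wording and programming. If made as a protocol amendment, the change needs ethics re-review and approval, as Ethical Considerations requires. Recruitment is still under way and analysis follows the two-year follow-up, so there is time to make it before outcomes are analysed.

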### Follow-Up and Assessments

Participants in both study groups will undergo prospective monitoring comprising two phases: (1) on-treatment assessment (from enrollment to 1 month after treatment completion) and (2) posttreatment assessment (up to 24 months after randomization). On-treatment assessments will involve standardized clinical evaluations, including physical signs, laboratory testing, medication adherence (pill counts and self-reporting), and safety monitoring, and will be scheduled at week 2, month 1, and month 2 for the 1H_3_P_3_ arm, and at week 2, then monthly until month 4 for the 3HR group. On the basis of recommendations from the independent protocol review board, and to comprehensively evaluate the impact of interventions on quality of life, a protocol amendment was implemented after approximately 2300 participants had been enrolled. Following ethics committee approval, the EuroQol 5-Dimensions 3-level questionnaire (version 6.0, December 2018) was incorporated as an exploratory end point. This questionnaire will be administered at every on-treatment assessment for participants enrolled after the amendment’s effective date. Posttreatment assessment will focus on active TB surveillance as well as delayed AE monitoring and will occur every 6 months from randomization until study exit. At each visit, participants will receive a standardized symptom screening for active TB, including persistent cough (≥2 weeks), fever, night sweats, weight loss, hemoptysis, or other TB-associated symptoms. Participants with positive symptom screens will undergo confirmatory sputum culture and molecular diagnostic testing. The end point adjudication committee will determine the final active TB diagnosis per predefined criteria.

The schedule of this study is summarized in Table 2.

**Table 2. T2:** SPIRIT (Standard Protocol Items: Recommendations for Interventional Trials) diagram showing enrollment, intervention, and assessment procedures.

	Enrollment	Allocation	Postallocation phase						Closeout
Time point^a^	–30 days	0 day	2 weeks	1 month	2 months	3 months	4 months	Every 6 months	24 months
Enrollment									
Eligibility screening	✓								
Informed consent	✓								
Medical history	✓								
Allocation		✓							
Interventions									
1-month isoniazid plus rifapentine 3 times weekly regimen		↔^b^	↔	↔					
3-month daily isoniazid plus rifampicin regimen		↔	↔	↔	↔	↔			
Assessments^c^									
Demographic characteristics and medical history	✓	✓							

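### Per-protocol entry requires 90% of doses, so TB found during treatment is removed over about 81 days in 3HR but 25 in 1H3P3, tilting that analysis modestly against 1H3P3

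*Protocol article*

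**What the plan says.** Two analysis sets are prespecified in the Statistical Analysis section of the protocol article. The modified intention-to-treat set takes everyone randomized who had at least one dose. For the other, "the per-protocol population includes all randomized participants who completed ≥90% of scheduled doses within 110% of the planned treatment duration", and there must also be no major deviation; taking prohibited anti-TB drugs is listed as one.

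Under TPT Intervention, "the intervention arm will receive a 12-dose 1H_3_P_3_ regimen, and the active control arm will receive a 90-dose 3HR regimen". The Statistical Analysis section turns the 90% rule into doses and weeks: "≥11 doses within 6 weeks for the 1H_3_P_3_ group and ≥81 doses within 16 weeks for the 3HR group".

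Under Study Objectives and End points, the outcome is a "composite of bacteriologically confirmed or clinically diagnosed active TB within 24 months after randomization", so TB that appears during the course counts. It can also be found then. Follow-Up and Assessments says "At each visit, participants will receive a standardized symptom screening for active TB", and on-treatment visits fall at week 2, month 1 and month 2 in both arms, with months 3 and 4 added for 3HR.

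The article nowhere exempts a participant whose course was cut short by the primary event, and it does not start per-protocol follow-up at a time common to both arms.

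**The concern.** Membership of the per-protocol set is settled by something that happens after the outcome clock has started. A participant who is diagnosed with TB and stops preventive dosing before dose 11 (1H3P3) or dose 81 (3HR) cannot meet the rule. The outcome then decides who is analysed, over a period about three times as long in the control arm. TB found at month 2 would normally count in 1H3P3 and be dropped from 3HR.

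This differs from the familiar selection of adherent participants. It remains when adherence is perfect in both arms, because it comes from the difference in course length. At stake is one of only two prespecified analyses of the noninferiority question. It could show 1H3P3 as worse than 3HR when the regimens are equal.

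**Working it through.** **Inputs from the article.** 12 and 90 doses; 90% completion rule; 24-month (730-day) end point from randomization; 2.1% incidence in both arms (7% untreated, 70% efficacy); 1584 per arm before attrition; margin of a 20% relative loss of efficacy.

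**Assumptions.** Preventive dosing stops at TB diagnosis; adherence is otherwise perfect; true risks are equal; the hazard is constant unless stated.

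1. *The article's dose thresholds.* 0.9 × 12 = 10.8, so 11 doses; 0.9 × 90 = 81 doses. Both match the article.
2. *When the thresholds are reached.* Dose 11 at three per week comes at about day 25 (11/3 × 7 = 25.7 days; day 24 on a Monday-Wednesday-Friday pattern from day 1). Dose 81, taken daily, comes at day 81.
3. *Margin as a ratio.* Efficacy 0.8 × 70% = 56%; incidence 7% × 0.44 = 3.08%; 3.08/2.1 = 1.467; ln 1.467 = 0.383.
4. *Expected events.* 1584 × 0.021 = 33.3 per arm.
5. *Cases found as they arise.* Share removed: 25/730 = 3.4% in 1H3P3 and 81/730 = 11.1% in 3HR, or 1.1 and 3.7 events (net 2.6). Ratio = (1 − 0.034)/(1 − 0.111) = 1.09. Share of the log margin: 0.083/0.383 = 22%. Solving the large-sample Cox score equation with day 24 in place of day 25 also gave 1.09.
6. *Cases found only at scheduled visits.* The last visit before the threshold is week 2 in 1H3P3 and month 2 in 3HR. Share removed: 14/730 = 1.9% and 60/730 = 8.2%, or 0.6 and 2.7 events (net 2.1). Ratio = (1 − 0.019)/(1 − 0.082) = 1.07. Share of the log margin: 0.066/0.383 = 17%.
7. *Early events (assumption).* If half of the 24-month events fall evenly in the first 6 months (182.5 days), the shares are 0.5 × 25/182.5 = 6.8% and 0.5 × 81/182.5 = 22.2%. Ratio = 0.932/0.778 = 1.20.
8. *Lower bound.* If no TB arises between about day 25 and day 81, both arms lose the same share and the ratio stays at 1.00.
9. *Common landmark.* In a simulation of 200,000 per arm with equal risks, starting follow-up in both arms at day 112 left the hazard ratio within about 1% of its all-participant value, both under a constant hazard and with events concentrated early (Weibull shape 0.5).

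The frailty term in the planned model ("Cox proportional hazards regression model with shared frailty terms and exact likelihood estimation") deals with clustering. It does not create or remove this effect.

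**The case against.** The strongest objection is that the decisive step is not written down. The discontinuation list under TPT Intervention does not mention a TB diagnosis, and a case who went on to take all doses without a major deviation would stay in the set. A reader might infer that the set can contain only people who were TB-free until they finished; the article does not support that certainty. What remains is that the stated rule has no exemption, active TB is an exclusion criterion for the trial, and taking prohibited anti-TB drugs is a second possible route out. The rule is also presented as an explicit definition, so it is more than a detail left to an analysis plan.

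Second, the effect is small in the plainest case. With a design effect of 1 + 3 × 0.05 = 1.15, the standard error of the log hazard ratio is √(1.15 × 2/33.3) = 0.263, so a shift of 0.083 is about 0.3 standard errors. That stands. A reader might also infer that half the margin or more is used up, but that needs early event timing, which the documents neither support nor exclude. Nor should a loss of power be read off here: whether the sample size supports the stated margin is a separate matter.

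Third, the bias runs against noninferiority, and the modified intention-to-treat set keeps every event. Both statements are right. One might infer that a valid noninferiority result would be overturned, but the article does not require the two sets to agree, so that consequence depends on a decision rule it does not state.

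**Conclusion.** The point holds as a modest, one-directional distortion of the per-protocol analysis. With equal true risks, perfect adherence and dosing that stops at diagnosis, the per-protocol hazard ratio sits at about 1.07 to 1.09 under a constant hazard. It would be about 1.20 if half the events came in the first 6 months, and 1.00 if none came between about day 25 and day 81. The direction follows from the article's own definitions once dosing is assumed to stop at diagnosis; the size depends on event timing that the article does not give. The distortion cannot create a false noninferiority claim and leaves the modified intention-to-treat result alone. It can make the two prespecified analyses differ for a reason unrelated to how well the regimens work.

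**What to change.** Amend the per-protocol definition so that a participant whose only reason for not completing is a primary event or death is not excluded. Judge adherence as at least 90% of the doses scheduled up to that date, and do not count anti-TB treatment given for that event as a major deviation.

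Add a sensitivity analysis that starts per-protocol follow-up in both arms at one common landmark after both completion windows, so at 16 weeks or later, among those still TB-free.

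The cost is a sentence or two and one extra analysis. Dose dates are already logged in the diaries, although the article gives residual drug counts priority where sources disagree, so adherence up to the event needs a stated source.

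Each part has a downside that the plan should state. Judging adherence only to the event keeps early cases with short exposure, while event-free non-completers are still dropped. Suppose, as an assumption, 65% completion in 3HR with dropout spread evenly over the course, and 92% in 1H3P3. Early 3HR cases are then retained at about 82.5% against 65% for others, a relative event rate of 0.889 + 0.111 × 0.825/0.65 = 1.030. For 1H3P3 it is 0.966 + 0.034 × 0.96/0.92 = 1.001. The ratio is 1.001/1.030 = 0.97, a small bias the other way. The landmark analysis avoids this but discards early events and departs from the end point counted from randomization. The two should therefore be reported and read together.
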